##### Type 1 error protection

To help control for Type 1 error, the Benjamin Hochberg (BH) method will be used to adjust for the multiple comparisons proposed in the current study [49]. The BH method adjusts for multiple comparisons by controlling false discovery rate instead of family-wise error rate. It is less conservative than the more traditional Bonferonni methods, yet still provides adequate protection against Type 1 error. Since its inception, there has been growing evidence suggesting that the BH method is the optimal solution to the multiple comparison problem in most practical situations.

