#### Observational ratings

##### Observational coding

Video recordings of SP practice interactions and SP test case interactions for all participants are coded by a research team using an objective observational coding measure with five domains of skills related to the training: non-anxious and empathic presence, assessment of risk factors, assessment of protective factors, asking about suicidal ideation and behavior, and safety planning. Initial development work established acceptable inter-rater reliability using Gwet’s AC1 statistic, which is considered preferable to Cohen’s Kappa in cases when raters produce ratings that are not necessarily statistically independent [30]. Participants are also rated (“needs work,” “acceptable work,” and “good work”) on a general quality item (e.g., degree of collaboration, tone).

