### Statistical analysis

#### Data processing

Data collection and storage is managed by REDCap, a secure software system supported by the institution. (Data management procedures are fully described in the study manual.) A baseline check of randomness will be conducted for each demographic and outcome variable collected. Because we are interested in establishing equivalence (as opposed to detecting differences), a more conservative alpha level will be applied (α = .20). Categorical variables will be analyzed using chi-square tests; continuous variable differences will be assessed using a general linear model approach (ANOVA). Any baseline difference will be controlled for statistically in all subsequent analyses. For analyses related to hypotheses, α = .05 and covariates will include stratification variables of gender and residency/NP training program, race/ethnicity, age, and the specific outcome baseline score as well as any other variables found to differ at baseline. Effect sizes (Hedge’s *g*) will also be examined for each of the study hypotheses.

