The primary hypothesis of the study is that participants in the experimental condition will demonstrate significantly better skills compared to the control group, as measured by reliable, observed ratings of behaviors in the SP assessment at 6 months. We will use ANCOVA to assess SP training effects at follow up on all participants’ skills. Skills will be measured by reliable observational ratings of several suicide specific and general interviewing skills. In all instances, gender, training program group, race/ethnicity, and age will be included as covariates to aid in statistical power [35, 36].

##### Exploratory analysis for hypothesis 3

We will examine statistical equivalence between the two SP modalities (face-to-face; telehealth). Similar to Hypothesis 1 (above), Tryon’s inferential confidence intervals will be used to assess for equivalency among face-to-face and telehealth modalities [31, 32]. Following Treadwell and colleagues [33], a standardized small effect of .20 [34] will define the criterion for establishing a MID. As a form of sensitivity, a MID of .10 will also be examined. As a second form of sensitivity, multilevel modeling will be used to decompose the variance associated with these observed training outcomes into variance attributed to the person as well as variance attributed to time (first SP interaction, second SP interaction) and variance attributed to modality. Since the order is randomized, we might expect more variance attributed to time (improving over time). Within these models, the learner (person) defines level 2 with the observed ratings being the dependent level one variables. Both time and modality will be entered as time varying covariates.

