##### Power analyses

Optimal Design software [43] was used to assess statistical power. As previously stated, covariates will be included in all models to help improve power to detect a treatment effect [35, 36]. Power will be computed on a modest effect size estimate of .30. With a minimum final sample size of 108 participants and explaining 40% of the variance in the outcome, we have .51 power to detect an effect size of .30. However, power increases to .80 if 50% of the outcome variance is explained by covariates. If 60% of the outcome variance is explained via covariates, we have greater than .80 power to detect an effect size of .20. We believe that an effect size of .30 is attainable and we also expect that baseline values of the dependent variable of interest as well as other baseline variables are likely to account for 50% of the variance in the dependent variable. While we recognize that power will be more limited for the exploratory questions addressed (and will supplement all analyses with the use of effect sizes), we do feel that the knowledge gleaned will provide useful information with regard to dissemination of the simulation training — addressing whether implementation via telehealth is statistically equivalent to in-person implementation as well as providing preliminary knowledge about the amount and predictors of change over time.

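### No single primary skills score is named, and the Benjamini-Hochberg rule does not set the primary hypothesis apart, so on the plain reading the primary result depends on secondary results

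*Protocol article*

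**What the plan says.** All places are in the protocol article.

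- Hypothesis 3, under Hypotheses and exploratory analyses, identifies the primary question: "The primary hypothesis of the study is that participants in the experimental condition will demonstrate significantly better skills compared to the control group". The method is ANCOVA at follow-up, and "Skills will be measured by reliable observational ratings of several suicide specific and general interviewing skills". The covariate sentence that follows is worded for more than one model.
- Observational coding describes an "objective observational coding measure with five domains of skills related to the training", plus a separate three-level general quality item. No total across domains is defined there. By contrast, the Transfer of training section does name the sum of its 8 items as a composite.
- Data processing sets the test level: "For analyses related to hypotheses, α = .05".
- Type 1 error protection states that "the Benjamin Hochberg (BH) method will be used to adjust for the multiple comparisons proposed in the current study". It adds that the method "adjusts for multiple comparisons by controlling false discovery rate instead of family-wise error rate" and calls the resulting protection adequate. It does not set the primary hypothesis apart, list families or give the false discovery rate level.
- Power analyses gives power for 108 participants under several values of explained variance, for example "we have .51 power to detect an effect size of .30" when 40% is explained. It does not mention multiplicity.

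**The concern.** Benjamini-Hochberg is a step-up rule: the more tests in a family succeed, the looser the threshold for the rest. If the skill ratings share a family with knowledge, satisfaction, self-efficacy and the other outcomes, two things follow. Success on outcomes that say nothing about observed skill makes a skill finding easier to declare. Failure on those outcomes makes it harder.

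The primary hypothesis then has no error rate of its own, and its power is not that of a single test at .05. Because no single skills score is named, a reader also cannot tell which result, or how many results, would count as confirming the primary hypothesis.

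**Working it through.** **Inputs from the article.** N = 108 allocated 1:1, so 54 per arm; effect size .30; 50% of variance explained as the planning case; α = .05; five domains plus one quality item.

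**Assumptions.** Two-sided tests; false discovery rate level .05; each of the 6 ratings tested separately; 5 other tests in the same family (the Hypothesis 1 time effect, and the Hypothesis 2 outcomes of satisfaction, self-efficacy, intention and use), so 11 in all; equal correlation of 0 or .5 between test statistics.

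**1. The plan's own power figure.** The noncentrality is d/√(1−R²) × √(54/2).
- R² = .40: .30/√.60 × √27 = 2.01. Power at two-sided .05 with 105 df is .514, which agrees with the stated .51.
- R² = .50: .30/√.50 × √27 = 2.20. Power is .589 (.597 by the normal approximation). The article states .80 here. That gap is a separate matter; .59 is used below as the unadjusted reference.

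**2. How the threshold moves.** With k other tests certain to succeed, the first skill rating to pass needs p ≤ .05 × (k+1)/11.
- k = 0: .05/11 = .0045
- k = 1: .05 × 2/11 = .0091
- k = 5: .05 × 6/11 = .0273

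Hand check for independent ratings with no true effect: 1 − (1 − .0273)⁶ = .153 for k = 5, and 1 − (1 − .0091)⁶ = .053 for k = 1. The step-up rule adds slightly to these.

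**3. Chance of at least one false skill finding** (simulation, 200,000 replicates, six null skill ratings):

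| Other tests in the family | Correlation 0 | Correlation .5 |
|---|---|---|
| 5 null | .029 | .031 |
| 1 certain, 4 null | .055 | .050 |
| Hypothesis 1 certain, four Hypothesis 2 tests at d = .30, R² = .50 | .099 | .081 |
| 5 certain | .154 | .120 |
| 5 certain plus 14 null | .072 | .064 |

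The 14 extra null tests stand for the Hypothesis 1 group and interaction tests (2) and four moderators for each of the three outcomes in the Hypothesis 2 ANCOVA list (4 × 3 = 12).

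**4. Power per rating** when all six ratings carry d = .30 at R² = .50: about .40 if the five others are null and about .56 if they are clearly positive, against about .59 for one unadjusted test.

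**5. Alternative readings.**
- One skills score inside a study-wide family with 5 to 10 other tests: type I error .005-.013 if the others are null and .047-.050 if strongly positive; power .27-.34 and .59-.60 respectively.
- Benjamini-Hochberg applied to the six skill ratings alone: chance of any false finding .044-.050; power per rating about .50; no dependence on secondary results.

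**The case against.** The article defines no family. Adjustment within each hypothesis also fits its sentence, and the dependence on secondary results would then vanish. Nor does it say that six ANCOVAs will be run: it describes one coding measure with domains, and a single score would remove the inflation. A condensed article may leave both points to a full protocol or analysis plan that is not shown. The article is also open about controlling the false discovery rate, so judging it by any false finding among the skill ratings applies a stricter standard than it claims. These objections stand, and they limit the point to a conditional one.

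Three stronger readings are tempting but not supported.

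- A reader might infer that the near-certain knowledge gain under Hypothesis 1 inflates the primary error rate by itself. In the 11-test family one certain positive gives only .050-.055.
- A reader might infer that power falls to .25, the value at .05/11. That is only the first step of the procedure; if all six ratings improve and the others are null, it is about .40 per rating.
- A reader might take .12-.15 as the expected error rate. It needs all five other outcomes to be certain while skill is exactly null, and a larger family with many null tests brings it to about .06-.07.

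What remains is that the article states a rule and a scope, does not exempt the primary hypothesis, and names no primary score. This goes beyond omitted detail, because the claim of adequate protection rests on that rule.

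**Conclusion.** The point holds in conditional form. On the plain reading of the Hypothesis 3 and Type 1 error protection sections, the primary result depends on secondary results. In the assumed 11-test family, the chance of a false skill finding runs from about .03 to .12-.15 according to how the other five tests turn out, with .08-.10 in an intermediate case built on the article's own effect size. Power per rating runs from about .40 to .56, and the power paragraph does not allow for this.

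The size rests on the assumed family, six separate rating tests, a level of .05 and correlations of 0 to .5. Inflation above .05 requires several skill ratings in a shared family. A single score in that family keeps type I error at or below about .05 and loses only power. The documents do not show that the primary error rate is inflated under every reading, only that the stated rule does not protect it.

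**What to change.** In Hypothesis 3, name one primary skills score at the 6-month test case, for example a total across the coded domains, and test it once at two-sided .05 outside the Benjamini-Hochberg family. If the domains are to stay co-primary, apply Benjamini-Hochberg or a family-wise method to the skill ratings alone.

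In Type 1 error protection, restrict the remaining adjustment to the secondary tests, and report the exploratory analyses as estimates with confidence intervals.

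The cost is a few sentences and no change to data collection. If a single score is chosen, the domain-level results become secondary. If the ratings stay co-primary, power per rating is about .50 rather than .59 in the planning case.

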## Discussion

This RCT examines the benefit of practice via realistic standardized patient (SP) simulation interactions with feedback as part of training in suicide prevention skills. Objective ratings of suicide risk assessment and safety planning for primary care providers-in-training will contribute to an evidence base for the effectiveness of simulation practice and feedback over and above video-based expert teaching. Given the data that show primary care is a critical site for suicide prevention, well trained and competent primary care providers are essential to reducing the prevalence of primary care patients who die by suicide.

Already, the logistics for scheduling the resident learner group has been an unanticipated, practical dilemma. It is important to note that the residency and NP training program directors agreed to embed the suicide prevention education experiences into their curriculum for second year trainees. Our proposed training timelines for both conditions and learner groups are designed to mirror real-world circumstances where providers are not likely to encounter a patient at risk for suicide immediately following video-based expert teaching in suicide prevention. Therefore, we planned SP practice encounters for the experimental group within four months of completing video-based modules so that both the experimental and control groups could experience the “test case” at around 6-month follow-up. However, many of the residency rotations are not able to support time for the resident-SP encounters, which has posed challenges for scheduling SP sessions for the experimental participants. Four rotations relevant to suicide prevention (i.e., adolescent outpatient, ambulatory pediatrics, developmental behavioral pediatrics, practice-based elective rotations) offered times to complete SP sessions. So far, timing of these rotations for some residents in the experimental group has been less consistent with the study timeline. Residents in the control group pose far fewer logistical challenges.

Participants in both conditions are aware that the simulated patient interaction is part of the suicide prevention training program. Therefore, bias is not likely to impact condition comparisons because it is the same for all participants. We acknowledge, however, that trainees are likely to be more alert to suicide risk and management than in usual practice.

Rigorous observational coding of participant suicide prevention skills is underway. However, we have already realized that we similarly need to measure actor-educator fidelity to the SP character and feedback procedures. Although the 14 SPs are rigorously trained and tested for adherence to character and procedural standards prior to working in the study, there is likely to be variability in their interactions. Additionally, there may be drift in adherence to standards over the course of the study. A fidelity measure (noted in the measures section above) has been developed and added to the coding efforts which will enable us to analyze for the effect of actor fidelity on participants’ demonstrated skills.

Finally, during our first group of subjects, we learned that several participants from the nurse practitioner program attended an unrelated seminar on suicide prevention, which occurred while they were completing activities for our training program. This prompted us to add an item to the final training survey that asked participants how many hours of additional (i.e., not including our training) concurrent suicide prevention training they received since beginning the training. Doing so allows us to account for possible skill improvement due to other parallel training.

## Abbreviations

CTL-PC: Commitment to Living for Primary Care
PCP: primary care provider
SP: standardized patient
